
#### **Inclusion Criteria:**

Inclusion criteria will be: (1) systemically healthy individuals, (2) presence of gingival inflammation in more than 30% of the sites (GI=1), (3) presence of 28 20 fully erupted permanent teeth, excluding third molars and teeth indicated for exodontia, (4) willingness to adhere to the study protocol.

#### **Exclusion Criteria:**

Exclusion criteria for the present study: (1) pregnant or lactating women, (2) systemic involvement that could interfere with the results of the study (e.g. diabetes mellitus, immunological disorders), (3) intake of antimicrobials and/or anti-inflammatories in the last 6 months and probiotics or oral antiseptics in the last month, (4) use of medication with gingival implications, (5) history or presence of periodontitis, (6) presence of non-plaque-induced gum disease, (7) known allergies to the experimental materials, (8) presence of orthodontic appliances, (9) extensive prosthetic involvement, (10) smoking, (11) legally incapacitated patients.

#### **Risks:**

The risks present refer to the discomfort the patient will experience when undergoing the gold standard periodontal treatment for gingivitis (prophylaxis and/or supragingival scraping). The use of tablets containing placebo or probiotics will not pose any risk to the patient's health.

#### **Benefits:**

Balancing the intestinal flora

#### **Data Analysis Methodology:**

The normality and homoscedasticity of the data obtained will be verified. Inter- and intra-group comparisons at different time intervals will be carried out using appropriate parametric or non-parametric tests. A significance level of 5% will be used for all statistical analyses. All calculations will be carried out using SPSS software (SPSS, Chicago IL, USA).

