#### **Proposed Methodology:**

Consent for the research (Free and Informed Consent Form), submission of the project to the CEP; Sample calculation (total = 60, n = 30); Selection of patients (FORP-USP Postgraduate Clinic); All patients will undergo a full-mouth periapical radiographic examination. The volunteers will be grouped into an oral hygiene program (OHP) according to their specific needs.

In this program, patients will receive instructions for effective plaque self-control, including information on the Bass technique (BASS, 1954) and interproximal cleaning with dental floss. They will also be encouraged to brush the back of the tongue once a day and will receive a toothbrush and the same toothpaste to be used throughout the trial period (Colgate Total®, Anapol Ind. Com. Ltda - Kolynos do Brasil - Colgate Palmolive Co., São Bernardo do Campo, SP, Brazil).

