Before starting the study, the selected individuals will be identified by a numerical code. According to a random numerical table generated by a computer program, the study coordinator will allocate each patient to one of the following experimental groups: control (placebo) or test (probiotic therapy). The volunteers will not know which experimental group they belong to. One week before the initial collections (-1s), all patients included in the study will receive prophylaxis and/or supragingival scraping, as necessary. On day 0, all subjects will receive tablets with the same composition, texture, shape and flavor, except for the presence of the probiotic. In the test group, the 10 mg tablets will contain 109 colony-forming units (CFUs) of *Bifidobacterium animalis* subsp. *lactis* HN019. Subjects will be instructed, immediately after their first consultation (baseline), to consume the tablet once a day for 8 weeks. They will be instructed to always consume the gum after the last brushing, before going to bed, letting the gum dissolve in the mouth. During the 56 days in which they consume the tablets, the volunteers will also be instructed to keep the tablets in the fridge, not to consume any other probiotic product and not to use any chemical plaque control product, with the exception of dentifrice. After 28 days of starting daily intake of *Bifidobacterium animalis* subsp. *lactis* HN019, the patients will be instructed to return for collection of new clinical data, and they will have to spend 8 hours prior to the examination without any hygiene measures, with the exception of the tablets, (AYALA, et al.; 2016). Participants will be instructed to maintain their oral hygiene routine throughout the study. Clinical periodontal, immunological and microbiological parameters will be assessed in three periods: at baseline (pre-intervention period), 28 days after the start of probiotic or placebo administration and 56 days after the start of probiotic or placebo administration. Clinical periodontal examinations will be carried out by a single trained and calibrated examiner, who will be unaware of the experimental groups to which each volunteer belongs. The examiners of the immunological and microbiological evaluations will also be blind to the experimental groups of the samples analyzed. The probiotic and non-probiotic (placebo) tablets will be prepared by a compounding pharmacy and both will have the same format and will be packaged in identical bottles. The tablets will be sent to the study coordinator, who will mark each patient's numerical code on a set of 56 tablets (the amount to be consumed by each individual over 8 weeks), according to the experimental group to which they belong. The coded packs will be sent to the study's clinical examiner, who will distribute them to the patients and at no time will have any information about their contents. (See the rest in the project file).

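### The between-group test is left to a normality check on the collected data, and no baseline-adjusted comparison is named although every parameter is measured at baseline

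*Protocol*

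**What the plan says.** The only analysis text in the protocol is the short Data Analysis Methodology section. It begins with a check on the data: "The normality and homoscedasticity of the data obtained will be verified". It continues: "Inter- and intra-group comparisons at different time intervals will be carried out using appropriate parametric or non-parametric tests". The error level follows: "A significance level of 5% will be used for all statistical analyses". The section names no model, covariate, change score or effect measure.

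Proposed Methodology shows which data are available: "Clinical periodontal, immunological and microbiological parameters will be assessed in three periods: at baseline (pre-intervention period), 28 days after the start", and again at 56 days. Each patient should therefore have a pre-intervention value for each parameter. That baseline comes after professional cleaning: "One week before the initial collections (-1s), all patients included in the study will receive prophylaxis and/or supragingival scraping, as necessary".

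The sample size appears only as "Sample calculation (total = 60, n = 30", with no effect size, SD, power or correlation. The Hypothesis section sets out a between-group question: better results in the probiotic arm than in the control arm.

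**The concern.** There are two linked weaknesses.

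- **The form of the test depends on the data.** Read as written, the section inspects the outcome data and then chooses a parametric or a rank-based test. Secondary outcome lists plaque index, gingival index, probing depth, attachment level, bleeding, microbiology and six cytokine measurements, with two follow-up visits each. The quantity compared could be a difference in means for one outcome or visit and a comparison of ranks for the next. The results would then lack a common effect measure.
- **No between-group analysis that uses baseline is named.** The intra-group comparisons would presumably use baseline, but they do not estimate the difference between arms, which is what the hypothesis concerns. If the between-group tests use only the day 28 or day 56 value, the variation between patients that baseline could explain stays in the error term.

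With 30 patients per arm, a baseline covariate that has already been measured is one of the few ways to gain precision without new data.

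**Working it through.** **Inputs from the protocol.** 30 per arm; alpha 0.05 (sidedness not stated, two-sided assumed); baseline, day 28 and day 56 measured.

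**Inputs assumed.** Correlation r between baseline and follow-up of 0.3, 0.5 and 0.7. The protocol gives no value.

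**The plan's own figure.** The total of 60 cannot be reproduced, because none of its inputs is stated. Solved backwards with the normal formula, the difference detectable at 80% power is

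d = (1.960 + 0.842) × √(2/30) = 2.802 × 0.258 = 0.723 SD.

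With the t distribution it is 0.736 SD. These are benchmarks for what follows, not the protocol's target difference.

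**Effect of adjustment.** ANCOVA multiplies the variance of the group difference by 1 − r². Power at d = 0.723 SD is Φ(2.802/√(1 − r²) − 1.960). The unadjusted sample size with the same precision is 30/(1 − r²) per arm.

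| r | Variance remaining | Reduction | Power | Detectable difference (80% power) | Equivalent n per arm |
|---|---|---|---|---|---|
| 0.3 | 0.91 | 9% | Φ(0.977) = 83.6% | 0.690 SD | 33 |
| 0.5 | 0.75 | 25% | Φ(1.275) = 89.9% | 0.626 SD | 40 |
| 0.7 | 0.51 | 49% | Φ(1.963) = 97.5% | 0.517 SD | 59 |

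With the t distribution at the same 0.723 SD, unadjusted power is 78.7% and ANCOVA gives 82.3%, 88.9% and 97.1%.

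**Change scores.** The variance factor is 2(1 − r) = 1.4, 1.0 and 0.6. Power is 66%, 80% and 95%. Change scores beat the follow-up value alone only when r exceeds 0.5, and they stay below ANCOVA at all three values. The protocol does not say that change scores will be used; they are shown only as one possible reading of the section.

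**Simulation.** 4,000 trials per scenario with normal data and 30 per arm. The two-stage procedure was a Shapiro-Wilk test in each arm, then Mann-Whitney if either was significant and a t-test otherwise, on the follow-up value.

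| r | Power, two-stage | Power, ANCOVA | Type I error, two-stage | Type I error, ANCOVA |
|---|---|---|---|---|
| 0.3 | 78.3% | 81.3% | 4.65% | 4.75% |
| 0.5 | 78.2% | 88.4% | 5.35% | 5.00% |
| 0.7 | 78.3% | 96.6% | 4.70% | 5.38% |

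The Monte Carlo standard error at 5% is √(0.05 × 0.95/4000) = 0.34 percentage points, so the type I error rates are compatible with 5%. The simulation does not cover skewed data.

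**The case against.** The strongest objection is that the section does not exclude baseline adjustment. ANCOVA and repeated-measures ANOVA can both count as suitable parametric methods, and the reference to time intervals does not have to mean separate tests at each visit. Naming models and covariates is ordinary SAP content. The SAP is not shown, and Proposed Methodology itself sends the reader to a fuller project file. This much stands: a reader might infer that the plan rejects adjustment and throws the baseline away, and the text does not support that. The missing covariate would not be a finding on its own. What remains is that the section does fix something, namely that a check on the collected data precedes the choice between parametric and rank-based tests. A SAP that follows it would inherit that rule.

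The second objection is that the gain may be small. Baseline is taken one week after cleaning, so the correlation with later values may be modest; at 0.3 the gain is about 4 points of power. This also stands, and it is why only a range can be given.

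The third is that an unadjusted comparison in a randomised trial is valid. That is correct. A reader might infer that chance baseline imbalance biases the comparison or that the pre-test inflates false positives. Randomisation already allows for chance imbalance in the error rate, and the simulation with normal data showed no inflation.

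**Conclusion.** The point holds as a matter of efficiency and of pre-specification. The protocol lets the collected data choose between a parametric and a rank-based comparison, and it names no baseline-adjusted between-group analysis although the baseline values are planned for every parameter. If follow-up values alone are compared, the variance of the group difference is larger than it need be. ANCOVA would remove 9% to 49% of it for correlations of 0.3 to 0.7, a gain of about 4 to 18 points of power at the difference detectable with 80% power. These sizes rest on the assumed correlations, a linear relation with baseline, a two-sided 5% test and complete data on 30 per arm. The cost of a target that can switch between means and ranks is one of interpretation, and no size is attached to it. The documents do not support a claim of bias or of inflated error rates. This is a change that should be made; it is not a flaw that invalidates the trial.

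**What to change.** In Data Analysis Methodology, replace the pre-test switch with one named, baseline-adjusted model for each continuous outcome, analysed on patient-level values. Two forms would serve:

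- ANCOVA of the day-56 value on group and baseline; or
- a linear mixed model for days 28 and 56 with group, visit, group-by-visit and baseline value.

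Choose any transformation in advance, for example the log for cytokines. Report the adjusted day-56 group difference with its 95% CI. Distribution checks can stay as model diagnostics, but should not decide which test is used.

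The cost is revised wording and slightly more analysis work. No new data are needed, and SPSS, the software already named, can fit these models. Timing needs care. The justification for the amendment says that the clinical data are already collected, and the execution schedule placed the statistical analysis in February to April 2019. The change should therefore be dated before unblinding. If the codes are already open, it should be labelled a revised analysis.

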#### **Primary outcome:**

Project Submission Date: 27/10/2020

File Name: PB\_INFORMAÇÕES BÁSICAS\_1654788\_E2.pdf

Project Version: 4

**Secondary outcome:**

Turesky Plaque IndexGingival Index (LOE & SILNESS, 1963)Clinical probing depth (mm)Clinical insertion level (mm)Bleeding on probing, assessed dichotomously (AINAMO & BAY, 1975)Microbiological composition of the biofilm by checkerboard DNA-DNA hybridizationAbsolute quantification of *Bifidobacterium animalis* subsp. *lactis* HN019 in the biofilm by qPCRQuantification of cytokines (pg/l) IL-1, IL-1, IL-8, RANTES, MCP-1, MIP-1

**Sample size in Brazil:** 60

**Recruitment countries**

| Country of origin of the study | Country | No. of survey participants |
|--------------------------------|---------|----------------------------|
| Yes                            | BRAZIL  | 60                         |

**Other information**

**Will secondary data sources (medical records, demographic data, etc.) be used?**

No

**Report the number of individuals personally approached, recruited, or who will undergo some kind of intervention at this research center:**

60

**Groups into which the research participants at this center will be divided**

| Group ID                                               | No. of individuals | Interventions to be carried out                                                                                                                               |
|--------------------------------------------------------|--------------------|---------------------------------------------------------------------------------------------------------------------------------------------------------------|
| Control (gold standard periodontal therapy)            | 30                 | Prophylaxis and/or supragingival scraping, consumption of placebo tablets and additional periodontal treatment (if necessary) at the end of the experiment.   |
| Test (gold standard periodontal therapy and probiotic) | 30                 | Prophylaxis and/or supragingival scraping, consumption of probiotic tablets and additional periodontal treatment (if necessary) at the end of the experiment. |

**Is the Study Multicentric in Brazil?**

No

**Do you propose waiving the ICF?**

No

**Will samples be retained for bank storage?**

No

**Execution schedule**

| Stage identification                                                                                                               | Start (DD/MM/YYYY) | End (DD/MM/YYYY) |
|------------------------------------------------------------------------------------------------------------------------------------|--------------------|------------------|
| Preparation of abstracts for presentation at national and international conferences                                                | 01/05/2019         | 30/08/2019       |
| Immunological analysis                                                                                                             | 01/08/2018         | 01/01/2019       |
| Clinical, immunological and microbiological monitoring                                                                             | 01/08/2018         | 01/01/2019       |
| Final report on the activities carried out                                                                                         | 01/05/2019         | 30/08/2019       |
| Statistical analysis of the data obtained                                                                                          | 01/02/2019         | 30/04/2019       |
| Data collection                                                                                                                    | 01/03/2018         | 02/07/2018       |
| Clinical, immunological and microbiological monitoring                                                                             | 01/05/2018         | 02/07/2018       |
| Patient screening-Partial procurement of consumables                                                                               | 01/08/2017         | 02/07/2018       |
| Preparation of abstracts for presentation at national and international conferences                                                | 28/02/2019         | 31/05/2019       |
| Preparation of manuscripts for publication in journals with a selective editorial policy classified A1 in the CAPES Qualis system. | 01/05/2019         | 30/08/2019       |

|                             |            |            |
|-----------------------------|------------|------------|
| Partial activity report - 1 | 02/07/2018 | 31/07/2018 |
| Microbiological analysis    | 01/08/2018 | 01/01/2019 |

#### Financial Budget

| Budget identification                                            | Type  | Value in Reais (R\$) |
|------------------------------------------------------------------|-------|----------------------|
| Gracey Curets                                                    | Costs | R\$ 1.500,00         |
| Toothpaste (Colgate)                                             | Costs | R\$ 500,00           |
| Consumables (paper, xerox, printing, clinical, laboratory, etc.) | Costs | R\$ 5.000,00         |
| PCR                                                              | Costs | R\$ 3.500,00         |
| Clinical Periodontal Probes                                      | Costs | R\$ 500,00           |
| Toothbrushes (Colgate)                                           | Costs | R\$ 800,00           |
| Checkboard                                                       | Costs | R\$ 30.000,00        |
| Luminex                                                          | Costs | R\$ 30.000,00        |
| Total in R\$                                                     |       | R\$ 71.800,00        |

| Proof of Receipt                                  | PB_COMPROVANTE_RECEPCAO_964740.pdf                  |

Finish

Keep the entire research project confidential: Yes

Term: 2 years

Justification for the amendment:

All the clinical data of the patients in this research project has already been collected and the clinical procedures of the study have been completed. Samples of dental biofilm were collected for microbiological analysis. The microbiological analysis that had been submitted to the Research Ethics Committee aimed to verify the microbiological composition of the biofilm by means of checkerboard DNA-DNA hybridization and the absolute quantification of *Bifidobacterium animalis* subsp. *lactis* HN019 in the biofilm by qPCR. However, the opportunity arose to carry out a more complete microbiological analysis of the biofilm samples using next-generation sequencing technology. I declare that this will not influence patient care or the collection of their samples, which have already been carried out.

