#### **Secondary Objective:**

In patients with generalized gingivitis, with oral administration of probiotics or placebo, evaluate:

Clinical parameters: plaque index, gingival index, gingival bleeding index, clinical probing depth, clinical insertion level, bleeding on probing; Levels of the cytokines IL-1, IL-1, IL-8, RANTES, MCP-1 and MIP-1 present in gingival crevicular fluid, using enzyme immunoassays (LuminexTM xMAP®);

Biofilm microbiota, by checkerboard DNA-DNA hybridization;

Detection and quantification of *Bifidobacterium animalis* subsp. *lactis* HN019 in biofilm by Polymerase Chain Reaction (qPCR).

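### Sequencing is added after data collection, but the listed microbiota outcome is still checkerboard, and the protocol does not say whether sequencing replaces or supplements it

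*Protocol*

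**What the plan says.** The justification for the amendment, at the end of the Protocol, states that "All the clinical data of the patients in this research project has already been collected". It recalls that the microbiological plan submitted earlier consisted of checkerboard for biofilm composition and qPCR for the administered strain. It then reports that "the opportunity arose to carry out a more complete microbiological analysis of the biofilm samples using next-generation sequencing technology". It does not withdraw checkerboard, does not call sequencing an addition, and names no sequencing outcome.

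The page footer under Primary outcome dates this version: "Project Submission Date: 27/10/2020" (version 4). In that version:

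- The Secondary Objective reads "Biofilm microbiota, by checkerboard DNA-DNA hybridization". The Summary and the Secondary outcome section likewise give checkerboard as the composition assay. qPCR appears in all three, but only for detecting or quantifying the study strain.
- The Financial Budget has lines for checkerboard (R$ 30.000,00) and PCR (R$ 3.500,00), and none for sequencing.
- Data Analysis Methodology says: "Inter- and intra-group comparisons at different time intervals will be carried out using appropriate parametric or non-parametric tests". It adds: "A significance level of 5% will be used for all statistical analyses".
- The Execution schedule places microbiological analysis at 01/08/2018 to 01/01/2019 and the stage "Statistical analysis of the data obtained" at 01/02/2019 to 30/04/2019. It has no sequencing stage.

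**The concern.** The assay that defines a listed outcome belongs in the protocol's objectives and outcomes. Here the reason given for the amendment and the sections it should have changed disagree, and a reader cannot tell which assay will supply the microbiota result.

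The change also comes after the clinical data and samples were in hand. A result from a method chosen at that stage could be reported as though it were the protocol's planned microbiota outcome. Sequencing can also yield many taxa, while the only error rule in the protocol is one 5% level for everything, with no order among analyses and no adjustment. What is at stake is how far a reported microbiota difference between probiotic and placebo can be believed. The microbiota is a secondary outcome, so the clinical conclusions are not directly affected.

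**Working it through.** **1. Is sequencing anywhere in the operative text?** The Summary, Secondary Objective, Secondary outcome, Execution schedule and Financial Budget do not mention it. The budget lines add up to the printed total: 1,500 + 500 + 5,000 + 3,500 + 500 + 800 + 30,000 + 30,000 = 71,800 reais. So sequencing is not a line lost from the table.

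**2. Reading A: sequencing supplements checkerboard.** The only error rate in the documents is 5%. The number of tests per method, their sidedness and their correlation are not given. I assume one global two-sided test per method.

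- Independent tests: 1 − (1 − 0.05)² = 1 − 0.9025 = 9.75%.
- Bound under any dependence: 0.05 + 0.05 = 10%.
- Correlated tests: both methods use the same participants' biofilm, so correlation is likely. With jointly normal statistics, the chance is 1 − P(|Z₁| < 1.96 and |Z₂| < 1.96):

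| Assumed correlation | Chance of at least one false positive |
|---|---|
| 0 | 9.75% |
| 0.5 | 9.1% |
| 0.7 | 8.35% |
| 0.9 | 7.0% |
| 0.99 | 5.7% |

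If both follow-up visits (days 28 and 56) were tested by both methods and all four tests were independent, the chance would be 1 − 0.95⁴ = 18.5%. Repeat visits are correlated, so that figure is a high-end illustration.

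**3. Reading B: sequencing replaces checkerboard.** There is then one composition analysis and no inflation of the kind in step 2. But the outcome listed in the Secondary outcome section will not be produced, and the one that will be produced has no stated measure or visit. This is a change of outcome after data collection.

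**4. Either reading, if taxa are tested one by one.** Expected false positives per comparison = (number of null taxa) × 0.05. For 100 taxa this is 5; for 200 it is 10. The expectation does not need independent tests. The number of taxa is an assumption, because the protocol gives none and does not say that testing will be by taxon.

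**5. After the fix.** With one named outcome and one test, the false-positive chance on that outcome is 5.0%. If both methods were kept as outcomes at 2.5% each, it would be 1 − 0.975² = 4.94% for independent tests, and at most 5.0%.

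**The case against.** **The wording may mean replacement.** The justification describes checkerboard as what had been submitted, turns with a 'however', and calls sequencing more complete. On that reading there are no competing analyses. This is fair: a reader might infer that two rival analyses definitely exist with a free choice between them, and the text does not establish that. But replacement leaves the listed outcome wrong, so the contradiction remains.

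**Other files may settle it.** The attachments include an amendment form and a detailed project file, neither of which is shown, and either may define the sequencing outcome. That stands as a limit. The current objective and outcome sections would still need to match.

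**Multiplicity and modelling belong in the analysis plan.** Largely so, and a plan may exist. A 5% level is also compatible with adjusted p-values. The protocol does fix one level for all analyses, however, and requires no adjustment, so the rule gives no protection as written.

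**Laboratory blinding is already covered.** Proposed Methodology keeps the microbiological examiners blind to group, so nothing further is needed there.

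**The timing is disclosed.** The justification says openly that clinical data collection was complete. It does not say whether group codes or results were known.

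**Conclusion.** The inconsistency is real and needs correcting, at the level of a secondary outcome. Under supplementation, the false-positive chance for the microbiota question rises from 5% to between 5.7% and 9.75% over correlations from 0.99 to 0, assuming one global test per method. Under replacement, the listed outcome is not produced and its successor is undefined. Taxon-by-taxon testing at an unadjusted 5% would add about 5 expected false positives per 100 null taxa per comparison.

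Two stronger readings are not supported:

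- A reader might infer that sequencing was chosen with the codes open, because statistical analysis was scheduled to end on 30/04/2019, about 18 months before this version. Those are planned dates. The protocol does not say that codes were opened or that any results had been seen. It only leaves the question unanswered.
- A reader might infer that part of any microbiota shift would be an artefact of reads from the administered strain lowering the share of other taxa. The protocol gives no read share and does not say that relative abundance will be the measure. This is a possibility worth a sensitivity analysis, not a finding.

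**What to change.** 1. In the Summary, Secondary Objective, Secondary outcome and Financial Budget, state whether checkerboard is kept or withdrawn.
2. Name one microbiota outcome before any comparison of sequencing data between groups.
3. Label sequencing as added after data collection and exploratory. If checkerboard is withdrawn, report sequencing as a change of outcome made after data collection.
4. State whether group codes or any results were known when sequencing was chosen.
5. For taxon-level tests, replace the unadjusted 5% rule with Benjamini-Hochberg control of the false discovery rate at 5%.
6. Adjust group contrasts for the baseline sample, which the design already collects.
7. Optionally, repeat the sequencing analysis with reads assigned to the administered species removed.

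The cost is text edits to an amendment already being submitted and minor analysis work. No new samples or visits are needed. The downside is that the sequencing results carry exploratory status.
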